**All concomitant medications will be carefully documented and considered in the interpretation of clinical outcomes.**

The following psychiatric medications are prohibited in participants receiving psilocybin due to known or potential pharmacodynamic interactions and risk of attenuated psychedelic effects or adverse reactions:

•Monoamine oxidase inhibitors (MAOIs)

•Tricyclic antidepressants (TCAs)

•Benzodiazepines ≤ 2 mg lorazepam equivalents per day (must not be taken within 12 hours prior to psilocybin administration)

•Antipsychotics

•Lithium

Participants will undergo a thorough medication review during screening to identify potential pharmacological interactions. Medications with prohibited serotonergic activity require washout periods of 2–4 weeks before psilocybin dosing according to clinical practise guidelines.

- Participants who cannot safely discontinue contraindicated medications will not be included in the study.

- The washout will primarily be monitored by phone and a medical doctor within the research team appointed by the principal investigator, with in-person visits if needed. Participants who exceed the 8-week limit without dosing will be re-evaluated for eligibility by the principal investigator. The time from screening to first dosing shall not exceed 8 weeks regardless of washout status.

- Psychotherapy and other non-pharmacological treatments will be allowed throughout the study period as TAU if not deemed an exclusion criterion. Temporary daycare after discharge will be considered part of TAU rather than non-pharmacological treatment.

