**Clarification on Targeted Sample Size for Dosing**

The trial aims to dose at least 20 participants in the psilocybin treatment arm. This number refers to participants who receive at least one 25 mg psilocybin session, not only those who are randomized.

Analysis of safety and tolerability will primarily focus on this dosed cohort.

Recruitment will continue until a minimum of 20 participants in the intervention arm have received at least one dose, unless safety or feasibility concerns require early termination.

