6.2 Exclusion Criteria

- Psychosis, bipolar disorder, substance use disorder, family history of psychosis or bipolar disorder, refusal of birth control, lifetime psychedelic use.
- Cardiovascular conditions,
  - Resting systolic blood pressure >140 mmHg or diastolic blood pressure >90 mmHg at screening or baseline.
  - Clinically significant arrhythmias, tachycardia and QT prolongation.
  - History of stroke, myocardial infarction, or other significant cardiovascular events.
  - Seizure disorders or history of epilepsy.
- Diabetes mellitus, positive drug tests, suicidal intent, allergy or intolerance to drug content, blood or needle phobia.
- Metal pieces in the body (contraindicated by fMRI, assessed in each case by MR-technician)
  - Only for the MRI-part of the study
- Any other clinically significant medical condition that, in the investigator’s opinion, may pose a risk to the participant or interfere with study results.
- Care under the Swedish Compulsory Psychiatric Care Act (LPT).
- Ongoing treatment with medications that have clinically relevant 5-HT2A-receptor antagonistic properties and are therefore expected to directly block or substantially interfere with the pharmacodynamic effects of psilocybin. Such medications require an appropriate washout period prior to psilocybin administration, based on pharmacokinetic properties and clinical judgement. Medications without direct 5-HT2A-antagonistic effects are not excluded on this basis**.**
- Sustained weight restoration, defined as BMI > 21.0 for ≥ 6 consecutive months within the 12 months prior to screening, as documented in medical records.

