7.2 Auxiliary Medicinal Products

- None planned.

- In cases of significant distress or adverse reactions during dosing sessions, adjunctive medications such as benzodiazepines (e.g., lorazepam) may be administered at the discretion of the study physician. These instances will be documented and reported to monitoring oversight and safety monitoring committee.

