7.3 Concomitant Use of Other Medicinal Products and Treatments

Concomitant use of psychiatric medications may be permitted if not listed below and if deemed safe by the principal investigator.

**Participants receiving ongoing treatment with antipsychotic medications or lithium will generally not meet the inclusion criteria for this study, as such treatments typically indicate psychiatric conditions that are exclusionary according to the protocol and/or involve pharmacological mechanisms that are incompatible with psilocybin administration.**

**In cases where the underlying diagnosis does not in itself constitute an exclusion criterion, and a participant is receiving a medication with clinically relevant 5-HT2A-receptor antagonistic properties off-label or for other non-exclusionary indications, the investigator may, together with the participant, carefully assess the feasibility of dose reduction or discontinuation. If dose reduction or discontinuation is not clinically appropriate or feasible, the participant will not be included in the study.**

**Tricyclic antidepressants (TCAs) exhibit clinically relevant 5-HT2A-receptor antagonistic properties. Ongoing treatment with TCAs is rare in the target population. In the rare event of TCA treatment, careful clinical assessment must be undertaken to evaluate the medical necessity and feasibility of discontinuation. If dose reduction or discontinuation is not clinically appropriate or feasible, the participant will not be included in the study.**

**Mirtazapine, which has pronounced 5-HT2A-receptor antagonistic effects, may be considered for gradual tapering and discontinuation prior to psilocybin administration. If dose reduction or discontinuation is not clinically appropriate or feasible, the participant will not be included in the study.**

**Antihistamines with 5-HT2A-receptor antagonistic properties will be assessed on a case-by-case basis. As these medications are typically prescribed on an as-needed basis, temporary discontinuation prior to dosing is generally feasible.**

**Selective serotonin reuptake inhibitors (SSRIs) and serotonin–norepinephrine reuptake inhibitors (SNRIs) do not exhibit direct 5-HT2A-receptor antagonism and are therefore not prohibited per se.**

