7.4 Treatment After Trial End

- Participants will return to standard clinical care after the trial concludes. No continuation of psilocybin treatment is planned.

A transition plan will ensure continuity of care, including referrals to specialists or therapists for participants requiring additional support.

After the follow-up at six months, and once the safety committee has determined that safety and preliminary efficacy are satisfactory, participants in the active comparator arm will be offered the option to switch to the psilocybin intervention arm.

The switch to psilocybin treatment will follow the same preparation, dosing, and integration protocols as outlined for the intervention group.

8. Methods for Measurement of Endpoints for Clinical Efficacy and Safety

See attachment for complete list of measurement.

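### The benzodiazepine line in 7.3 contradicts the list it stands in: read literally, it bars low daily doses and leaves doses above 2 mg to discretion.

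*Protocol*

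**What the plan says.** Protocol section 7.3 opens with a default for psychiatric drugs: "Concomitant use of psychiatric medications may be permitted if not listed below and if deemed safe by the principal investigator". Later in the section comes the list that this default points to, introduced by "The following psychiatric medications are prohibited in participants receiving psilocybin due to known or potential pharmacodynamic interactions". Four entries are drug classes or single drugs without any dose: MAOIs, tricyclic antidepressants, antipsychotics and lithium. The fifth has a dose limit and a timing condition: "Benzodiazepines ≤ 2 mg lorazepam equivalents per day (must not be taken within 12 hours prior to psilocybin administration". After the list, 7.3 adds: "Participants who cannot safely discontinue contraindicated medications will not be included in the study".

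Elsewhere the protocol touches on benzodiazepines only indirectly or as rescue:

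- The medication criterion in 6.2 concerns 5-HT2A antagonists and states: "Medications without direct 5-HT2A-antagonistic effects are not excluded on this basis".
- 6.2 also excludes positive drug tests, without saying whether a prescribed benzodiazepine counts.
- 7.2 covers distress during a dosing session: "adjunctive medications such as benzodiazepines (e.g., lorazepam) may be administered at the discretion of the study physician".
- 9.7 places benzodiazepines in the emergency kit.

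**The concern.** A dose limit in a list of prohibited drugs would normally bar what lies above it. This one bars what lies at or below it. The attached condition then regulates the timing of use that the heading has just forbidden. Someone applying the text cannot satisfy both the heading and the bracket.

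The line bears on who may be included and who may be dosed. The primary endpoint is the incidence of AEs and SAEs, and the list gives its own grounds as a weakened psychedelic effect or adverse reactions. If screening clinicians read the line differently, similar patients will be treated differently, and a monitor checking eligibility and treatment administration (11.2) has no single rule to check against.

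**Working it through.** No arithmetic applies. The check sets the rules side by side and asks what each possible reading requires at two example doses.

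**Inputs**

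1. Status of listed items: prohibited (7.3, introduction to the list).
2. Benzodiazepine entry: at most 2 mg lorazepam equivalents per day, with a 12-hour gap before psilocybin (7.3, list).
3. Default for unlisted psychiatric drugs: may be permitted if the principal investigator judges them safe (7.3, opening).
4. Consequence for someone who cannot stop a contraindicated drug: not included (7.3, after the list).

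**Readings**

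| Reading | 1 mg/day | 4 mg/day |
|---|---|---|
| A. The heading governs | Prohibited; not included if it cannot be stopped | Unlisted; principal investigator decides, no stated gap |
| B. The bracket governs, and only the stated range is covered | Allowed, with a 12-hour gap | Unlisted; principal investigator decides, no stated gap |
| C. The class is banned, with an exception at or below 2 mg/day | Allowed, with a 12-hour gap | Prohibited |

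**What follows**

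- At 1 mg/day, reading A gives the opposite decision to B and C.
- At 4 mg/day, C gives a ban where A and B give discretion.
- A follows the words most closely but leaves the 12-hour bracket with no function.
- B gives the bracket a function but ignores the heading.
- C gives both a function, but the reader has to supply the words that turn the dose into an exception.

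**Does another section settle it?** No.

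- The 6.2 medication criterion is confined to 5-HT2A antagonists and names no benzodiazepine dose.
- The 6.2 drug-test criterion sets no dose and does not address prescribed use.
- 7.2 and 9.7 concern acute treatment around dosing, not regular use.
- The washout of 2 to 4 weeks in 7.3 is tied to prohibited serotonergic activity and gives no benzodiazepine limit.

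**Could the sign be a text-extraction fault?** Unlikely. Comparison signs elsewhere come through as expected, for example in the 7% BMI criterion of 4.4 and the BMI criteria of 6.1 and 6.2.

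**The case against.** The strongest reply is reading C. The other entries are whole classes or single drugs, so the word benzodiazepines can be taken in the same way, with the dose and bracket as a compressed exception. A clinician may well read it so, and doses above 2 mg/day would then be barred. This stands as the likely intent. It also rules out two stronger conclusions that a reader might draw. One is that the inequality sign is proven to be reversed: the text cannot show whether the sign is wrong or an allowance was put in the wrong list. The other is that no rule exists for higher doses: under C they are banned, and under A and B the principal investigator's judgement still applies. What C does not do is remove the ambiguity, because the exception is nowhere stated.

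A second reply is that safeguards narrow the gap. 7.3 requires a thorough medication review at screening and documentation of all concomitant drugs, and 6.2 excludes substance use disorder and conditions that the investigator considers risky. This also stands. Unreviewed dosing of a high-dose user is unlikely, although none of these provisions sets a limit.

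A third reply is that the safety link is thin. A reader might infer that the line exposes participants to a dangerous combination. The protocol does not support that: it provides benzodiazepines as rescue and emergency medication during dosing, and it does not say which of the list's grounds applies to them. A weakened psilocybin effect is at least as plausible a reason for the entry.

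**Conclusion.** The point holds as a wrongly stated threshold, internally contradictory and open to conflicting application. Read literally with the default in 7.3, it bars daily doses of 2 mg lorazepam equivalents or less and leaves higher doses to discretion without the 12-hour gap. That literal result is probably not what was meant.

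Its size cannot be put in numbers. The protocol does not say how many participants are expected to use benzodiazepines; the number may be small and could be zero. The conclusion rests on the current wording of 7.3 and on the absence of any other benzodiazepine dose limit in the protocol. It does not depend on any assumption about harm. A dosing and eligibility limit belongs in the protocol, so an analysis plan would not be expected to resolve it. It should be corrected because the rule cannot be applied consistently as written, not because a particular harm has been shown.

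**What to change.** Replace the benzodiazepine entry in 7.3 with: *Benzodiazepines > 2 mg lorazepam equivalents per day are prohibited; ≤ 2 mg per day is allowed but must not be taken within 12 hours before psilocybin (rescue use under 7.2 excepted).* This is reading C written out. The sponsor should confirm that it is the intent; if the whole class is meant to be barred, the entry should say so and drop both the dose and the bracket.

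The cost is one line of text, with no added visits, data or analyses. Because the line touches eligibility and dosing safety, it may count as a substantial amendment under 12.2 and need approval from the Swedish Ethical Review Authority and through CTIS before use.

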7.4 Treatment After Trial End

- Participants will return to standard clinical care after the trial concludes. No continuation of psilocybin treatment is planned.

A transition plan will ensure continuity of care, including referrals to specialists or therapists for participants requiring additional support.

After the follow-up at six months, and once the safety committee has determined that safety and preliminary efficacy are satisfactory, participants in the active comparator arm will be offered the option to switch to the psilocybin intervention arm.

The switch to psilocybin treatment will follow the same preparation, dosing, and integration protocols as outlined for the intervention group.

8. Methods for Measurement of Endpoints for Clinical Efficacy and Safety

See attachment for complete list of measurement.

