4.2 Secondary Objectives

- To evaluate the efficacy of psilocybin with psychological support in reducing AN symptom compared to TAU and time to relapse within 12-month follow-up.

- To investigate potential mechanisms of action through neuroimaging (fMRI), using both resting-state and task-based paradigms for estimation, and biomarker analysis (BDNF levels) with in six-month follow-up.

- To assess changes in mental health, well-being, and personality traits within 12-month follow-up.

- To conduct a qualitative analysis of the subjective experiences of patients, their relatives, and therapists at last follow-up at 12 months.

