5.1 Overall Trial Design

- A Phase IIa, open-label, randomized controlled trial with two arms:

1. Active treatment arm; Two dosing sessions with psilocybin 25mg with psychological support alongside TAU.

2. Active comparator control arm; TAU only.

TAU includes specialized care offered in an eating disorder unit in Region Skåne, Sweden. If the active treatment arm is determined to be safe, tolerable, and preliminarily effective during the follow-up assessment, participants in the control group will have the option to switch to the active treatment while maintaining their usual specialized care.

This design minimizes ethical concerns regarding withholding a potentially effective treatment.

Participants will be randomly assigned (1:1) to either the intervention or control group.

Block randomization stratified by age group (16–17 and 18–35 years) will ensure balanced representation.

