***Halt and/or Early Termination Criteria***

Halt and/or Early termination may be initiated if any of the following occurs:

- Unacceptable or unforeseen safety concerns, including unexpected serious adverse reactions (SUSARs) or a pattern of adverse events suggesting increased risk.
- Insufficient recruitment, defined as fewer than 30% of the planned number of participants being enrolled within 18 months of trial initiation.
- Emerging external evidence (e.g. from other clinical trials or meta-analyses) indicating that the investigational product poses a significant safety risk or is no longer ethically justifiable to study.
- Ethical concerns raised by the Safety Review Committee, monitor oversight or regulatory authorities.
- Withdrawal of essential approvals, resources, or study drug availability.

In the event of early termination or temporary halt, all relevant regulatory authorities (including CTIS, Läkemedelsverket, and EPN) will be notified within 15 calendar days, as per applicable regulations. The reason for halt and/or early termination will be documented and explained in the final report.

Safety Review committee and monitor clearance will be required before resuming after a temporary halt not leading to and early termination.

- End of the Clinical Trial: When the last participant completes the last follow-up visit at week 52.

6. Subject Selection

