9.3 Reporting and Registration of Adverse Events

- AEs will be recorded by clinicians in the research team at each contact point with a study participant and reported in the REDCap documentation system and a manual standardized AE log template and serious events will be reported to the relevant authorities.

Serious adverse events (SAEs) will be reported within 24 hours of the investigator becoming aware, in accordance with Article 41 of CTR 536/2014.

- Suspected Unexpected Serious Adverse Reactions (SUSARs) will be reported to all investigators and Läkemedelsverket (LVM).

- All AEs and SAEs will be collected from Dosing 1 until final follow-up at 12 months.

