10.1 Analysis Population

- Both the Intention-to-treat (ITT) and per-protocol populations will be analysed.

ITT analysis will include all participants who are randomized, regardless of protocol adherence, to ensure generalizability.

Per-protocol analysis will focus on participants who completed the study as planned, ensuring the assessment of efficacy under ideal conditions.

The trial aims to dose at least 20 participants in the psilocybin treatment arm. This number refers to participants who receive at least one 25 mg psilocybin session, not only those who are randomized.

Analyses of safety and tolerability will primarily focus on this dosed cohort.

Recruitment will continue until a minimum of 20 participants in the intervention arm have received at least one dose, unless safety or feasibility concerns require early termination.

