**Data Retention and Security Measures**

- All study data will be retained for a minimum of 25 years post-study completion, as required by clinical trial regulations.
- Secure long-term storage will be ensured by Kliniska Studier Forum Söder in compliance with data archiving policies, and access will be restricted to authorized personnel only.
- Upon study closure, the database will be locked to prevent further modifications, and final datasets will be archived in compliance with EMA and national regulatory requirements.

15. Notification of Trial Completion, Reporting, and Publication

The study team aims to present the findings at psychiatry and psychedelic science conferences. Publish in high-impact journals focusing on psychedelics, psychiatry, neurology, and pharmacology. Press releases to major healthcare news outlets and the public. Host webinars, lectures and participate in forums for mental health professionals and researchers in Sweden. Share findings with collaborating academic institutions for further research and teaching. Release follow-up studies and long-term effect analyses.

CTIS will be reported in CTIS within one year after completion of study (six months follow-up of active arm and controls, not including the switch).

16. References

Barrett, F. S., Doss, M. K., Sepeda, N. D., Pekar, J. J., & Griffiths, R. R. (2020). Emotions and brain function are altered up to one month after a single high dose of psilocybin. *Scientific Reports, 10*(1), 2214. <https://doi.org/10.1038/s41598-020-59282-y>

Bates, M. L. S., & Trujillo, K. A. (2021). Use and abuse of dissociative and psychedelic drugs in adolescence. *Pharmacology Biochemistry and Behavior, 203*, 173129. https://doi.org/10.1016/j.pbb.2021.173129

Bogenschutz, M. P., Ross, S., Bhatt, S., et al. (2022). Percentage of heavy drinking days following psilocybin-assisted psychotherapy vs placebo in the treatment of adult patients with alcohol use disorder: A randomized clinical trial. *JAMA Psychiatry, 79*(10), 953–962. https://doi.org/10.1001/jamapsychiatry.2022.2096

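### TAU participants may switch to psilocybin after month 6, but endpoints compared between arms run to month 12 with no rule for post-switch data

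*Protocol*

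**What the plan says.** **The switch.** Section 7.4 states that, after the six-month follow-up and a favourable view of safety and preliminary efficacy by the safety committee, "participants in the active comparator arm will be offered the option to switch to the psilocybin intervention arm". It adds: "The switch to psilocybin treatment will follow the same preparation, dosing, and integration protocols as outlined for the intervention group". Section 5.1 gives the same option: "participants in the control group will have the option to switch to the active treatment while maintaining their usual specialized care". Section 8.2 places the six-month visit at week 24.

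**Horizons that extend past the switch.**
- Section 4.2 sets the efficacy objective as symptom reduction "compared to TAU and time to relapse within 12-month follow-up".
- Section 4.4 lists change in AN symptoms, well-being and personality at both 6 and 12 months.
- Section 4.3 makes AE and SAE incidence over the trial period the primary endpoint. Section 9.3 says: "All AEs and SAEs will be collected from Dosing 1 until final follow-up at 12 months". Section 10.2 compares the numbers and severity between groups, with risk or odds ratios.

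**Populations.** Section 10.1 states: "ITT analysis will include all participants who are randomized, regardless of protocol adherence". It also says that safety analyses focus primarily on participants who received at least one dose.

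**Completion.** Section 5.4 defines the end of the trial as: "When the last participant completes the last follow-up visit at week 52". Section 15 ties results reporting to "completion of study (six months follow-up of active arm and controls, not including the switch". Section 7.4 puts the month-6 switch under a heading about treatment after the trial has ended.

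**The concern.** From month 6 some of the control arm may have had the experimental treatment while still being analysed as controls. A 12-month comparison by randomised arm then no longer estimates psilocybin plus TAU against TAU alone. For efficacy, a real difference could be missed. For safety, which is the primary question, an excess of adverse events could look smaller than it is if events in switchers are tallied under TAU. If the rule is chosen only after switching has happened, the choice between keeping, dropping and censoring switchers can be influenced by the data.

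**Working it through.** The protocol gives no power calculation, effect size or event rate, so there is no figure of its own to reproduce beyond 2 × 20 = 40, which agrees. Timing comes from the protocol. The dilution figures rest on assumed inputs and show scale only.

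**1. Timing.** Section 5.2 puts Dosing 1 in week 1 and Dosing 2 in week 4. A TAU participant who starts the switch right after week 24 is dosed at about weeks 24 + 1 = 25 and 24 + 4 = 28. Both doses precede the 9-month and week-52 visits. Time after the first dose is 52 − 25 = 27 weeks, or 27/52 = 52% of follow-up.

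**2. Continuous outcomes.** Let *d* be the true 12-month difference in SD units and *s* the share of TAU that switches. If switchers gain the full effect at once, the ITT difference is *d*(1 − *s*). With n = 20 per arm and two-sided alpha 0.05, power ≈ Φ(*d*(1 − *s*)√(20/2) − 1.96).

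| *s* | *d* = 0.5 | *d* = 0.8 | Power for *d* = 0.8 |
|---|---|---|---|
| 0 | 0.50 | 0.80 | 0.72 |
| 25% | 0.375 | 0.60 | 0.48 |
| 50% | 0.25 | 0.40 | 0.24 |
| 75% | 0.125 | 0.20 | 0.09 |

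**3. Relapse.** Assume exponential times, a hazard ratio of 0.5, and the hazard in switchers changing at week 25. With an assumed TAU 12-month risk of 50%:
- psilocybin arm: 1 − 0.5^0.5 = 0.293
- a TAU participant who switches: 1 − 0.5^((25 + 0.5 × 27)/52) = 0.401
- risk difference: 0.500 − 0.293 = 0.207 with no switching, 0.451 − 0.293 = 0.158 at 50% uptake, and about 0.109 (unrounded inputs) if all switch.

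With an assumed TAU risk of 35% the differences are 0.156, 0.118 and 0.079. Relapse is diluted less than a month-12 score because events before the switch are untouched.

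**4. Adverse events, if switchers' events were counted under TAU.** Assume an any-AE risk of 90% if dosed and 40% on TAU. TAU-arm risk is 0.40(1 − *s*) + 0.90*s*. At 50% uptake this is 0.65, so the risk ratio falls from 0.90/0.40 = 2.25 to 0.90/0.65 = 1.38. At full uptake it is 1.00. With 80% and 30% the ratios are 2.67, 1.45 and 1.00.

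**5. Is there a rule that prevents this?** ITT keeps switchers in their arm. The per-protocol set is defined by completing the study as planned, and since the switch is permitted this does not clearly remove them. The sensitivity analyses in section 10.2 address missing data and antidepressant use. The six-month cut in section 15 concerns results reporting and leaves the 12-month endpoints of sections 4.2 and 4.4 in place. For adverse events, section 10.1 does not say whether switchers join the dosed cohort.

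**The case against.** The strongest reply is that the sponsor appears to regard the switch as lying outside the randomised comparison. Section 15 excludes it, section 7.4 files it under treatment after the trial, and section 5.2 labels week 9 the primary endpoint visit. Detailed handling may sit in an analysis plan that is not shown. The trial is a pilot with admittedly limited between-group power.

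Part of this stands. The switch is optional and committee-gated, so uptake before week 52 may be nil. Everything through month 6 is clean. But the 12-month horizons, the ITT rule, the AE window and the two completion points are all fixed in the protocol, and they conflict there.

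Several stronger readings are tempting and are not supported:
- *Switchers' adverse events will be counted as TAU events, so the primary safety result will understate risk.* No rule says so. Safety focuses primarily on the dosed cohort, and AE start dates and relatedness are recorded, so the events can be separated. It is an open risk.
- *The comparison could be reversed.* In every case calculated the movement is toward no difference.
- *Well-being at month 12 is contaminated.* Section 4.4 names that time point, but the 12-month visit in section 5.2 lists none of SWLS, PANAS or HILS. That is a separate inconsistency.
- *Response is affected.* Section 4.4 confines it to the treatment period.
- *Switchers' safety follow-up is cut off at their original week 52.* Section 7.4 does not say what follow-up applies to them.

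**Conclusion.** The concern holds for between-arm comparisons that extend beyond month 6: relapse, AN symptoms, personality, remission where it is assessed that late, and adverse events. Dilution is proportional to uptake for month-12 scores under the full-effect assumption, and milder for relapse. It is zero if nobody switches before week 52. At an illustrative 50% uptake, 0.8 SD becomes 0.40 SD, and a relapse risk difference of 0.207 becomes 0.158. These sizes rest on assumed effects, risks and uptake, because the protocol states none. For adverse events the finding is that switchers are unassigned, which leaves the comparison open to being pulled toward no difference. The conflict between sections 5.4 and 15 on when the study is complete needs no assumption. The matter should be settled before any participant switches.

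**What to change.** - State that all randomised between-arm comparisons (relapse, remission, EDE-Q, personality, adverse events) end at the six-month visit, before any switch.
- Present results from month 6 to month 12 within arm and descriptively. Cut TAU data at the start of the switch, and note that this censoring is informative, since those who switch are self-selected.
- Report adverse events after the switch as a separate switch cohort, not under TAU.
- Reconcile sections 4.2, 4.3, 4.4, 5.4, 7.4, 9.3 and 15 with this, including one definition of study completion and a statement of what follow-up applies to switchers.

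The cost is mainly wording in the protocol and any analysis plan, with no change to the sample size. The real loss is that there is no randomised 12-month comparison, which the switch already makes hard to interpret.
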